#### Phase II (second and third years)

As our main outcome is a binary variable, backward stepwise logistic regression analysis will be applied. This method will allow us to investigate whether the experimental condition is associated with the acquisition of the walking pattern. Analysis will be performed for each time measure. Changes in walking behavior over time will be analyzed by applying a Cox proportional hazards regression model for recurrent events. Using this methodology, we will estimate the hazard function of the outcome measure (the likelihood of walking over time). We will analyze differences between groups by introducing the experimental condition as a predictor of the moment in the longitudinal study when women maintained the walking pattern.

Randomization results will be checked to ensure that groups are comparable at the beginning of the study in terms of their distribution of potential confounding factors (walking pattern, IPAQ, FIQ, pain, age, emotional status and behavioral intention). The potential confounders will be selected according to previous analyses at baseline by applying confusion criteria (associations with exposition: *P* ≤ 0.20 and correlation coefficients >0.10; associations with the main result in CG: OR < 0.67 or OR > 1.5). Statistical adjustment to control for the impact of confounders on effect estimation will be applied by introducing them into the analyses (if changes in OR are greater than 10%). Effect modifiers of basal walking pattern will also be tested.

Multiple regression analysis will be performed for each secondary outcome variable. Baseline data will be introduced in the predictive model for each time measure. We will test the mediating effects of the behavioral intention and of implementation intentions in the total sample using path analysis.

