#### Randomization

We used a computer program to randomize the three experimental groups and four fibromyalgia associations, taking into account the size of each center
[40]. The 449 participants were allocated to the three experimental groups as follows: CG = 154, IG = 153 and MIG = 142 (Table 
1). We applied another computer program to generate random sequences to select the participants from each fibromyalgia association for the experimental and control groups
[41]. The randomization results will be checked by analyzing potential confounders such as walking patterns, physical activity, impact of FM, pain, emotional status and age (see the “Statistical analysis” subsection below).

**Table 1 T1:** **Randomized experimental group-center assignments**^
**a**
^

**Patient associations**	**Assignment, **** *n * ****(%)**			**Total**
	**CG**	**IG**	**MIG**	
ADEFA	7 (28.0)	9 (36.0)	9 (36.0)	25 (100)
AFEFE	42 (39.6)	29 (27.4)	35 (33.0)	106 (100)
AFIBROM	73 (33.2)	87 (39.5)	60 (27.3)	220 (100)
AFIBROTAR	32 (32.7)	28 (28.6)	38 (38.8)	98 (100)
Total	154 (34.3)	153 (34.1)	142 (31.8)	449 (100)

^a^ADEFA: Fibromyalgia Association of Alicante; AFEFE: Fibromyalgia Association of Elche; AFIBROM: Fibromyalgia Association of Madrid; AFIBROTAR: Fibromyalgia Association of Talavera de la Reina (Toledo); CG: Control group; IG: Implementation intention group; MIG: Motivation and implementation intention group.

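### The primary outcome is analysed by backward stepwise logistic regression with a data-driven confounder screen, which usually leaves out prognostic baselines and does not say that the arm is always kept

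*Protocol article*

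**What the plan says.** The Phase II part of the statistical analysis section opens: "As our main outcome is a binary variable, backward stepwise logistic regression analysis will be applied". The same procedure is the test of the treatment effect: "This method will allow us to investigate whether the experimental condition is associated with the acquisition of the walking pattern". It is repeated over follow-up: "Analysis will be performed for each time measure".

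Seven candidate covariates are named ("walking pattern, IPAQ, FIQ, pain, age, emotional status and behavioral intention"), and none is fixed in the primary model. Instead, "The potential confounders will be selected according to previous analyses at baseline by applying confusion criteria". The conditions are:

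- imbalance between arms: "associations with exposition: *P* ≤ 0.20 and correlation coefficients >0.10";
- an odds ratio with the outcome in CG below 0.67 or above 1.5;
- a change of more than 10% in the treatment OR, after which "Statistical adjustment to control for the impact of confounders on effect estimation will be applied by introducing them into the analyses".

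Baseline values are entered routinely only in the sentences on secondary outcomes. On allocation, the Randomization section says: "We used a computer program to randomize the three experimental groups and four fibromyalgia associations, taking into account the size of each center". Association is not among the seven candidates.

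**The concern.** The main hypothesis needs two fixed contrasts: the combined group (MIG) against CG, and MIG against IG. Backward elimination is a tool for building prediction models. Unless the arm is forced in, the procedure may remove the term the trial exists to estimate, or change what it is compared with.

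The covariate rule is a separate difficulty. After randomisation, an imbalance test measures chance only and does not identify prognostic variables. A rule that first requires imbalance discards useful baselines whenever they happen to be balanced. The CG and change-in-OR conditions use the outcome, so they can give different answers at 7 weeks, 3 months and 9 months. What is at stake is precision, a stable adjustment set and, under one coding of the arms, the meaning of the MIG estimate.

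**Working it through.** The plan gives no figure for the behaviour of this procedure, so there is none to reproduce.

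**Inputs from the protocol.** Rates of 10% (CG), 20% (IG) and 40% (MIG) and 115 women per group come from the sample size section. The analysis section reports 274 women attending; 274/3 ≈ 91 per arm, assuming an equal split.

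**Inputs assumed.** Removal level 0.10 (0.05 as a variant). One standard-normal baseline with OR 1.5, 2 or 3 per SD; 1,500 simulated trials per setting.

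**1. Imbalance condition.** Under randomisation, P ≤ 0.20 occurs with probability 0.20 whatever the prognostic strength. For seven independent candidates, 7 × 0.20 = 1.4 pass on average, and at least one passes in 1 − 0.8⁷ = 79% of trials.

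**2. All conditions required together.**

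| Baseline OR per SD | Enters the model | Left out |
|---|---|---|
| 1.5 | 5–7% | 93–95% |
| 2 | 13–16% | 84–87% |
| 3 | 17–20% | 80–83% |

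**3. Cost in power.** At assumed rates of 10/10/20% with baseline OR 3, the joint arm test has these powers:

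| Per arm | Fixed adjustment | Rule as written |
|---|---|---|
| 115 | 0.63 | 0.57 |
| 91 | 0.51 | 0.45 |

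At the protocol's own 10/20/40%, the joint test has power near 1 either way, so the loss does not show there.

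**4. Removal of IG, if the arms are separate indicators.** The chance of retention is the power of the IG versus CG test at the removal level:

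Φ{[(p₂ − p₁)√n − z√(2p̄q̄)] / √(p₁q₁ + p₂q₂)}, with p₁ = 0.10, p₂ = 0.20, p̄ = 0.15, q = 1 − p, z = 1.645.

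- n = 115: (1.072 − 0.831)/0.5 = 0.48, so retained 0.686 and dropped 31%.
- n = 91: (0.954 − 0.831)/0.5 = 0.25, so retained 0.597 and dropped 40%.
- With removal at 0.05, IG is dropped in 43% and 53%.

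Once IG is dropped, MIG is compared with CG and IG pooled. In simulation at 91 per arm its OR was then about 20% smaller than in the prespecified model (median ratio 0.80). When IG survives at 0.10, its average OR is 2.8 (n = 115) or 3.1 (n = 91), against a true (0.2/0.8)/(0.1/0.9) = 2.25.

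**5. Removal of the arm as one factor.** At 10/20/40% it is dropped in about 1% of fits or less. With no true effect it is dropped in about 90% at the 0.10 level.

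**6. Association.** From the counts in Table 1, chi-square = 8.67 on 6 df, P = 0.19, and Cramér's V = √(8.67/(449 × 2)) = 0.098. This would meet the P part of the protocol's own screen and just miss the correlation part. Table 1 covers the 449 women first selected, not the 274 who attended.

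**The case against.** **The arm is probably meant to stay.** The change-in-OR rule can be computed only with the arm in the model, and so can effect modification by baseline walking. Forced terms and removal levels are also details that a full protocol may settle. This stands as a reason not to say that the plan removes the arm: removal is left open, not stated. The 30–40% figure depends wholly on separate indicators and an assumed threshold. With a single factor under no effect, elimination amounts to a non-significant test, although it leaves no arm estimate in the final model.

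**The conditions may not all be required.** If only the 10% change rule applied, a baseline would enter in 26–33% (OR 1.5), 72–73% (OR 2) or 94–95% (OR 3) of trials. However, the text gives that rule after the selection criteria, so the joint reading is the natural one.

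**Two stronger readings are tempting, and neither is supported.**

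- A reader might infer that the CG screen lets noise into the model. For a 50:50 binary covariate with about 9 events in 91, SE(log OR) = √(2/4.55 + 2/40.95) = 0.70, so an unrelated covariate passes that single condition about 56% of the time. It must also pass the others, and an unrelated baseline meets all of them in under 1% of simulated trials.
- A reader might infer inflated type I error or invalid intervals. In 1,500 null trials the stepwise procedure rejected in 5.7% (95% interval about 4.5–6.9%), and the confounder screen alone in 5.0%. Neither shows clear inflation.

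**The group size is uncertain.** The 91 per arm is an assumption, since the Discussion plans to contact a further 180 women. The covariate result is much the same at 115.

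**Conclusion.** The concern holds in a limited form. The stated rule usually leaves out a prognostic baseline: about 80–95% of the time for OR 1.5 to 3 per SD, with all conditions required. It also lets the adjustment set vary by visit and gives up modest precision, about 0.06 in power in the assumed 10/10/20% case.

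The plan does not protect the arm term. This matters in about 30–40% of fits if the arms are separate removable indicators, and hardly at all if they form one factor and the expected rates hold. The baseline strengths, removal level, arm coding and equal split are assumptions. The case rests on precision, stability and a clear contrast, not on false-positive risk.

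**What to change.** Replace the stepwise procedure and the confounder screen with one prespecified logistic model, used unchanged at every visit:

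- arm as two indicators, always retained;
- patient association, because allocation was done by association;
- baseline walking pattern;
- any other baselines, such as behavioural intention, named before outcome data are seen.

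Report MIG versus CG and MIG versus IG from this model. Keep the baseline comparison of arms as description only. The cost is a change of wording and a few degrees of freedom; the baselines named here are already scheduled and association membership is known.

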This triple-blind study includes masking of the following groups in the manner described. Participants will know only that there are different intervention sessions but will not know the session contents; moreover, they will be unaware of the assumptions regarding the superiority of one intervention over another. Measures will be taken by researchers who do not participate in the treatment application and who are blinded to the experimental conditions. The statistician will also be blinded to the study protocol. The researchers who apply implementation intentions will also be blinded with respect to the MIG or IG experimental condition. In this phase, we aim to study the efficacy of the MIG intervention on unsupervised walking over the short term (7 weeks), medium term (3 months) and long term (9 months). The measurement at 7 weeks will be taken during the week after completion of the 6-week minimum walking program. We will base the selection of the medium- and long-term measurements on the assumption that the highest percentage of dropouts occurs between 3 and 6 months in supervised physical exercise programs
[8,9]. On the day of the intervention, a researcher will be responsible for the distribution of the participants into the three different treatment groups following random assignment. The researcher will remind participants of their confidentiality commitment.

Our main hypothesis is that a combined intervention (both motivational and volitional) will significantly increase walking behavior in comparison to the control group and that this effect will be higher than that in a merely volitional intervention in the short term and stable in the medium and long term.

Our selected walking pattern for FM patients is between two and four times weekly for about 50 minutes in bouts of 15 to 20 minutes, with a small rest between bouts to allow patients to avoid fatigue and continue the activity, for a minimum of six consecutive weeks

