#### Sample size calculation

We calculated the sample size for the experimental study by taking into consideration the 582 FM participants previously identified as the eligible population derived from the different associations: ADEFA (*n* = 33, 5.7%), AFEFE (*n* = 125, 21.5%), AFIBROM (*n* = 314, 54.0%) and AFIBROTAR (*n* = 110, 18.9%). The expected differential increase in the selected exercise prevalence from baseline is 10% for CG, 20% for IG and 40% for MIG. Given the rule that the frequency of dropouts should not exceed the frequency of the effect, we expect a maximum dropout rate of 30% before random allocation. This percentage will be added to the calculated sample size. We have defined the risk α as 5% and the study power as 80%. The minimum magnitude of the expected effect (in relation to the effect on CG) is 10% for IG and 30% for MIG. After we apply these conditions and dividing the sample population into three experimental groups, each group will consist of 115 persons, which is equal to 345 participants. In previously reported supervised programs of moderate-intensity walking, adherence has ranged from 62%
[14] to only 37.5%
[32]. In other studies, the percentage of patients who finished the supervised program was greater than 70% to 80%
[7,15,36-39]. In other words, studies have shown that more than 20% to 60% of patients do not complete physical activity programs which include walking. Therefore, we added a 30% dropout rate as a reasonable calculation, which gives us a sample size of 449 women with FM.

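### The primary analysis is framed as an association with the three-arm condition and is not tied to the two contrasts, MIG v CG and MIG v IG, that make up the main hypothesis

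*Protocol article*

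**What the plan says.** The main hypothesis is in the protocol article under Description of the overall project. The combined intervention "will significantly increase walking behavior in comparison to the control group", and "this effect will be higher than that in a merely volitional intervention in the short term and stable in the medium and long term". The same section defines short term as 7 weeks. So there are two comparisons, MIG v CG and MIG v IG, with the second tied to week 7 and later visits addressing stability.

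The analysis is under Statistical analysis, Phase II (second and third years): "As our main outcome is a binary variable, backward stepwise logistic regression analysis will be applied". Its purpose is to "investigate whether the experimental condition is associated with the acquisition of the walking pattern", and "Analysis will be performed for each time measure". For change over time a Cox model for recurrent events is added: "We will analyze differences between groups by introducing the experimental condition as a predictor". Neither sentence names a pair of arms, a reference arm or the result that would count as support for the hypothesis. The section does not say that condition is exempt from backward elimination.

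Expected effects appear in two places. Sample size calculation gives increases of 10% (CG), 20% (IG) and 40% (MIG), and adds: "The minimum magnitude of the expected effect (in relation to the effect on CG) is 10% for IG and 30% for MIG". Primary outcome measures gives MIG an expected advantage of 30% over CG and 10% over IG.

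**The concern.** Condition has three levels. Finding it associated with walking means only that the three rates are not all equal. That is compatible with IG and MIG being equally good and both better than CG, in which case the motivational session contributes nothing. It does not by itself establish MIG > CG either.

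The comparison with IG is what carries the claim that adding motivation to planning helps, a combination the article says is untested in fibromyalgia. If the criterion for success is not fixed to that comparison, then an overall association, a MIG–CG odds ratio, or the pattern of MIG significant against CG while IG is not, could each be offered afterwards as support. None of these is a test of MIG against IG.

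**Working it through.** **Inputs.** From Sample size calculation: 10/20/40% for CG/IG/MIG, α 5%, power 80%, 115 per arm (345 in total). From the Phase I results: 274 women attended the first evaluation session. Assumptions: the stated increases are treated as week-7 rates (eligible women do not meet the pattern at entry); tests are two-sided; 274/3 ≈ 91 per arm if split equally and all analysed; and, for the illustration only, the association is judged by a Pearson test on 2 df.

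**The plan's own figure.** 115 per arm does not reproduce from the stated rates. At two-sided 5% and 80% power the pairwise requirements are 199 (10 v 20%), 82 (20 v 40%) and 32 (10 v 40%) per arm. The 449 does follow from 345 × 1.3 = 448.5. This is a separate matter; 115 is used below as given.

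**Step 1: association test when MIG adds nothing over IG.** Take CG 10%, IG = MIG = 20%. The mean rate is 0.1667. The noncentrality is λ = n × Σ(p − p̄)² / [p̄(1 − p̄)] = n × 0.006667/0.13889 = 0.048n.
- n = 91: λ = 4.37; power at the critical value 5.99 is 45% (simulation 46%).
- n = 115: λ = 5.52; power 55% (simulation 57%).

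The simulations used 400,000 trials per setting and are the figures quoted elsewhere.

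**Step 2: other decision rules in the same setting.** Reading MIG significant v CG but IG not significant v CG as a win for MIG would be wrong in 16–17% of trials. Requiring both MIG > CG and MIG > IG, each at two-sided 5%, gives false support in about 2.1% (91) and 2.3% (115). With IG = MIG = 40% it is 2.5–2.6%. The ceiling is 2.5% in theory, apart from small-sample error, because MIG > IG must be significant in MIG's favour. Hence 2 to 3%.

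**Step 3: what an association result says about MIG v IG when MIG is better.**
- At 10/20/40%, the 2-df test is positive in over 99% of trials at either size. MIG > IG is not shown in about 15% (91) or 8% (115) of those positives.
- At 10/30/40%, it is again positive in over 99%. MIG > IG is not shown in about 70% (91) or 64% (115) of the positives.

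**Step 4: power of the two-contrast rule.** MIG v CG at 10 v 40% has power above 99.8% at both sizes, so joint power is in effect that of MIG v IG: Φ{[d − 1.96·√(2p̄(1−p̄)/n)] / √[(p₁(1−p₁)+p₂(1−p₂))/n]}.
- 20 v 40%, n = 115: (0.20 − 1.96 × 0.0604)/0.0590 = 1.38, 91.7%. n = 91: (0.20 − 1.96 × 0.0679)/0.0663 = 1.01, 84.3%. Simulated joint power: 92% and 85%.
- 30 v 40%, n = 115: (0.10 − 1.96 × 0.0629)/0.0626 = −0.37, 35.5%. n = 91: (0.10 − 1.96 × 0.0707)/0.0703 = −0.55, 29.2%. Simulated joint power: about 36% and 30%. For 80% power, 356 per arm would be needed.

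**The case against.** A reader might infer that the plan prescribes an omnibus test and that MIG is never compared with IG. The document does not support that. It names no omnibus or 2-df test. Describing a logistic model as investigating association is ordinary language. The confounder rule in the same section works on changes in the odds ratio, so group odds ratios will evidently be estimated, and the Cox sentence speaks of differences between groups. A logistic model with condition as a factor gives MIG v IG directly with suitable coding. Nor is the comparison overlooked elsewhere: Primary outcome measures attaches an expected difference to it.

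It can also be said that reference category, contrast coding and multiplicity rules belong in a statistical analysis plan that is not shown. That is right as far as coding goes.

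It is fair, too, that the 46–57% depends on a decision rule the article does not state and on an assumed 20% in both active arms. It illustrates what an association result can mean; it is not the plan's error rate.

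What stands is narrower. The article does state the question its primary analysis answers, and that question is not the main hypothesis. Expected effects are attached to both comparisons, but no test is attached to either.

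**Conclusion.** The concern holds in this form: the analysis can answer the main hypothesis, but the stated question and the absence of a success rule leave the two unconnected. A positive association result would not establish MIG > IG.

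Under the stated assumptions, a 2-df test would be positive in 46% (91 per arm) to 57% (115 per arm) of trials in which MIG adds nothing over IG, against 2 to 3% for the two-contrast rule.

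The power of that rule cannot be quoted as a single figure until the document settles the MIG–IG difference: about 85–92% at 20 points, about 30–36% if it is 30% v 40%. The 91 per arm is an assumption; the article does not state a Phase II analysed sample of that size. This should be corrected, but it does not call for a change of design or model.

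**What to change.** In Statistical analysis, Phase II, replace the association question with the following:
- The primary contrasts are MIG v CG and MIG v IG at week 7, from the logistic model for the full minimum walking criteria.
- Condition stays in the model and is not subject to backward elimination.
- The main hypothesis is supported only if both contrasts favour MIG at two-sided 5%. Because both must succeed, no alpha split is needed.
- The 3- and 9-month analyses address maintenance, and IG v CG is secondary.

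Reconcile the MIG–IG difference between Sample size calculation (20 points) and Primary outcome measures (10%), then state the power of the two-contrast rule for the number of women expected to be analysed.

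The cost is a few sentences of wording, with no new data or design change. The downside is that power for the main claim becomes that of MIG v IG, which is lower than for MIG v CG and would be poor if the 10-point difference is the intended one.

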### Description of the overall project

The study consists of two phases, both based on the same population.

Phase I, conducted over the course of 1 year, is a cross-sectional study with two measurement stages and the following three aims:

1. We will seek to gain access to the reference population, identify the eligible population, select the study population and identify the prevalence of our selected walking criteria (stage 1). The results of stage 1 are included in this paper.

2. We will seek to identify the predictors of the behavioral intention to carry out the selected walking program using the TPB and exploring the role of pain, impact of FM and fear of movement (stage 2).

3. We will seek to explore the concordance of walking behavior measurements (subjective and objective measures) (stage 2).

Phase II, which will be conducted over the course of 2 years, is an experimental, randomized, triple-blind study with two treatment groups and one active control group. Longitudinal measures will be taken at baseline and at 7 weeks, 3 months and 9 months of postexperimental intervention. One group will receive a motivational plus implementation intentions intervention (MIG), a second group will receive only an implementation intention intervention (IG) and the control group (CG) will be given a neutral task related to postural hygiene. The three groups will receive the same information on the benefits of physical exercise in FM. Motivational intervention will be based on the predictors of behavioral intention as measured and identified in phase I (stage 2) in order to create or strengthen the behavioral intention during the experimental study.

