#### Primary outcome measures

Two primary outcomes will be assessed as indicators of each intervention’s effect on exercise adherence:

1. We will measure the proportion of participants who perform the full minimum walking criteria (at least 30 minutes in bouts of 15 minutes with a small rest between bouts, twice times weekly over a minimum of 6 consecutive weeks) at the end of the 6-week period and the proportion of participants who have maintained it at 3 and 9 months. The expected efficacy of MIG is 30% higher than CG and 10% higher than IG.

2. Among participants who perform the full minimum walking criteria, we will focus on the proportion who reach the recommended pattern for FM patients at week 6 (between two and four times weekly for about 50 minutes in bouts of 15 to 20 minutes over a minimum of 6 consecutive weeks)
[31].

We will use the same self-reported measurements of the behavior from phase I (*ad hoc* self-reported items and daily logs) and pedometer readings.

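### The only model stated for change over time, a recurrent-event Cox model with one constant arm effect, does not suit a yes/no state defined at three fixed visits and cannot test whether the effect is stable to 9 months

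*Protocol article*

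**What the plan says.** Four parts of the protocol article bear on this point.

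- **Hypothesis** (Description of the overall project). The combined motivational and volitional intervention (MIG) is expected to increase walking relative to control (CG), and "this effect will be higher than that in a merely volitional intervention in the short term and stable in the medium and long term".
- **Visits** (same section). "Longitudinal measures will be taken at baseline and at 7 weeks, 3 months and 9 months of postexperimental intervention". Table 3 gives the follow-up visits as weeks 7, 20 and 43.
- **Outcome** (Primary outcome measures). The first primary outcome is the proportion meeting the minimum walking criteria "at the end of the 6-week period and the proportion of participants who have maintained it at 3 and 9 months".
- **Analysis** (Statistical analysis, Phase II). "As our main outcome is a binary variable, backward stepwise logistic regression analysis will be applied", and then "Analysis will be performed for each time measure". For the time course the section says: "Changes in walking behavior over time will be analyzed by applying a Cox proportional hazards regression model for recurrent events". It adds that "we will estimate the hazard function of the outcome measure (the likelihood of walking over time", and that groups will be compared by "introducing the experimental condition as a predictor of the moment in the longitudinal study when women maintained the walking pattern".

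No arm-by-time term, time-varying coefficient or contrast between visits is stated for either analysis.

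**The concern.** A recurrent-event Cox model needs events that happen at observed times and can happen again. Meeting the walking pattern is a state, and the outcome is defined at three visits. A woman who takes up the pattern and never stops has had one change of state. A recurrent-event model has either to count her again at each visit or to ignore her continued walking. The article's gloss on the hazard, as a likelihood of walking, describes the prevalence of a state and not the rate of an event.

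The second difficulty concerns the hypothesis. Proportional hazards with experimental condition as the predictor means one ratio per arm contrast, constant over follow-up. The durability part of the main hypothesis is a statement about whether the effect changes. A model that fixes the effect as constant assumes the answer, and its hazard ratio averages over the visits. If that ratio were read as evidence of a lasting effect, an early effect that had gone by 9 months could be reported in the same terms as a sustained one.

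**Working it through.** The article gives no numerical figure for this analysis, so there is none to reproduce. The check asks what the stated model would return under different time courses.

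**Inputs.** From the article: visits at weeks 7, 20 and 43; a binary outcome; arm as predictor; expected increases of 10% (CG) and 40% (MIG) from Sample size calculation; 274 women attending the first evaluation. Assumed here: the event is the pattern being met at a visit; risk intervals are 0–7, 7–20 and 20–43 weeks; ties are handled by Breslow's method; follow-up is complete; arms are equal in size; CG is at 10% at every visit. The three MIG time courses are also assumed.

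**Hazard ratio.** With d1j and d0j the MIG and CG events at visit j, and equal numbers at risk in the two arms at each visit, the Breslow score equation is

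Σ d1j = Σ (d1j + d0j) × HR/(1 + HR), so HR = Σ d1j / Σ d0j.

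Only the totals enter; the order of the visits does not. The CG total is 10 + 10 + 10 = 30 per 100 women.

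**Visit odds ratios.** The CG odds are 0.10/0.90 = 1/9. For MIG, 25% gives (1/3)/(1/9) = 3, 40% gives (2/3)/(1/9) = 6, and 10% gives 1.

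| MIG at week 7 / 3 months / 9 months | MIG total | HR | Visit ORs | 9-month minus week-7 difference (points) |
|---|---|---|---|---|
| 25/25/25% (stable) | 75 | 75/30 = 2.50 | 3 / 3 / 3 | 15 − 15 = 0 |
| 40/25/10% (lost by 9 months) | 75 | 75/30 = 2.50 | 6 / 3 / 1 | 0 − 30 = −30 |
| 10/25/40% (late) | 75 | 75/30 = 2.50 | 1 / 3 / 6 | 30 − 0 = +30 |

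**Sensitivity to follow-up.** With 100/85/70% at risk in both arms, the CG total is 10 + 8.5 + 7 = 25.5.

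- Stable: (25 + 21.25 + 17.5)/25.5 = 2.50
- Lost: (40 + 21.25 + 7)/25.5 = 2.68
- Late: (10 + 21.25 + 28)/25.5 = 2.32

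The ratios separate a little, but none of them shows whether the effect lasted.

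**Sensitivity to ties.** Another tie method would change the values. With complete follow-up and a constant CG rate, however, the partial likelihood is a product of three visit terms sharing one coefficient. Reversing the visit order leaves it unchanged, so the lost and late profiles still give one and the same ratio.

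**What a between-visit contrast would add.** Take 274/3 ≈ 91 per arm and, for simplicity, no within-woman correlation. The variance of a visit log OR is 1/(91·p1·(1−p1)) + 1/(91·p0·(1−p0)).

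- Lost effect: week 7 gives 1/21.84 + 1/8.19 = 0.168, and 9 months gives 2/8.19 = 0.244. The contrast is ln(1/6) = −1.79 with SE √0.412 = 0.64. The ratio of odds ratios is 0.17 (95% CI 0.05 to 0.59).
- Stable effect: each visit gives 1/17.06 + 1/8.19 = 0.181. The contrast is 0 with SE √0.361 = 0.60. The ratio of odds ratios is 1 (95% CI 0.31 to 3.25).

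The contrast therefore detects a complete loss of this size. Even under true stability, though, its interval is wide. Positive correlation between visits would narrow the intervals, and dropout would widen them.

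**The case against.** The strongest reply is that the plan does not depend on the Cox model alone. A reader might infer that the trial could not see an effect fade, or that the maintenance claim would rest wholly on a model blind to fading. The document does not support that. The same section plans logistic regression at each visit, and the primary outcome is itself defined visit by visit. Under the profiles above, those regressions would give 6/3/1 for the lost effect and 1/3/6 for the late one, so the pattern would be visible. This part of the reply stands. What it leaves open is a formal comparison between visits: a significant result at week 7 and a non-significant one at 9 months is not a test of change.

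A reader might also take it as settled that all events fall on three tied dates and that continued walking counts as a new event each time. The article does not define the event, the risk interval, the tie method or the recurrent-event variant. Daily logs and pedometers are scheduled at all three follow-up visits and could give finer timing within their recording windows. The article does not say that the Cox model will use them, and the primary outcome is defined at the visits. The coding above is therefore one plausible reading.

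The equal hazard ratios also follow from profiles chosen to have the same total. They show what the model can miss and do not predict what the trial will find.

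Finally, details such as proportionality checks or time-varying terms may sit in a fuller plan that is not shown. Their absence is not the point. The point is that the model the article does name is mismatched to the outcome and to the hypothesis.

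**Conclusion.** The concern holds in a limited form. The one over-time model that the article states treats a repeated binary state as a recurring event and, as described, assumes a constant arm effect. It therefore cannot test the hypothesis that the effect is stable to 9 months. The per-visit regressions describe each visit but include no stated contrast between them.

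On size: under the listed assumptions, time courses whose 9-month odds ratio is 3, 1 or 6 share a hazard ratio of 2.50. Incomplete follow-up moves the figures to between 2.32 and 2.68 without making them informative about stability. The mismatch itself does not depend on those assumptions; the particular numbers do. The change should be made because durability is part of the main hypothesis.

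**What to change.** Replace the Cox model with one repeated-measures logistic model (GEE or mixed) on the three follow-up visits, with terms for arm, visit, arm-by-visit, patient association and baseline walking pattern. From it, report:

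1. the MIG–CG and MIG–IG effects at each visit, with 95% confidence intervals;
2. for both comparisons, the 9-month-minus-week-7 contrast in effect, with its 95% confidence interval.

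Judge stability from the 9-month effect together with the interval for the contrast. A non-significant interaction alone is not proof of stability, as the width of the interval in the stable example shows. If the team wants to make a positive claim of stability, it should state before unblinding how large a loss of effect that interval must exclude; the article gives no such margin.

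The cost is a change of analysis wording. No new data or visits are needed, and the model can be fitted in the SPSS package already named.
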